### Study design

This will be a hospital-based, multicentre, individually randomized non-inferiority controlled trial.

Each woman will be randomized to receive either the full (AMTSL) package or the simplified package. The blinding of the intervention will not be possible because the comparison includes a manual procedure.

#### Interventions

In order to overcome the variations in the actual practice of AMTSL a working definition was discussed and agreed upon during the technical consultation.

#### Experimental arm: Simplified package

The simplified package will include;

##### • Uterotonic

Oxytocin 10 IU IM. Oxytocin will be administered as soon as possible after birth preferably within one minute. If a woman has an IV line oxytocin can be administered through the IV line by slow injection.

##### • Cord clamping

Cord will be clamped following observation of a uterine contraction either manually or visually. For practical purposes this is estimated to be around 1–3 minutes. It is recommended to clamp the cord close to the perineum.

##### • Placental delivery

Cord traction is omitted. Placenta should be delivered passively by aid of gravity and maternal effort. The caregiver should observe the placental separation and as the placenta delivers it should be held in two hands and gently turned so that the membranes do not tear off.

##### • Uterine massage

No uterine massage is recommended before placental delivery. After placental delivery the uterus will be rubbed and any clots expressed. For a period of two hours the uterus will be massaged gently until it contracts and this procedure will be repeated every 15 minutes. It is acknowledged that not all centres will be able to implement this component. Each centre will decide before the trial begins whether the uterine massage component will be implemented or not.

#### Standard intervention arm: Full AMTSL package

The full package will include:

##### • Uterotonic

Oxytocin 10 IU IM. Oxytocin will be administered as soon as possible after birth preferably within one minute. If a woman has an IV line oxytocin can be administered through the IV line by slow injection.

##### • Cord clamping

Cord will be clamped following observation of a uterine contraction either manually or visually. For practical purposes this is estimated to be around 1–3 minutes. It is recommended to clamp the cord close to the perineum.

##### • Placental delivery

Placenta will be delivered by controlled cord traction immediately after cord clamping and cutting. The cord will be gently pulled while applying counter traction to the uterus with the other hand. As the placenta delivers it should be held in two hands and gently turned so that the membranes do not tear off.

##### • Uterine massage

No uterine massage is recommended before placental delivery. After placental delivery the uterus will be rubbed and any clots expressed. For a period of two hours the uterus will be massaged gently until it contracts and this procedure will be repeated every 15 minutes. It is acknowledged that not all centres will be able to implement this component. Each centre will decide before the trial begins whether the uterine massage component will be implemented or not.

The two intervention packages will differ only in placental delivery technique. If the umbilical cord has been clamped early because of newborn indication cord traction should be applied only after the uterus has contracted as above.

#### Outcome measures

The primary outcome measure is blood loss of 1000 ml or more at one hour and up to two hours for women who continue to bleed after one hour. Blood collection will be made using the calibrated drape BRASSS-V^® ^and measured from delivery to one hour following delivery or up to two hours if bleeding continues [16].

Secondary outcomes are;

• blood transfusion,

• the use of additional uterotonics to treat PPH

• blood loss 500 ml or more

• postpartum maternal haemoglobin (in centres where feasible)

• maternal death

• manual removal of placenta,

• additional surgical procedures (e.g. hysterectomy, ligation of vessels)

• composite outcome of maternal death or severe morbidity (admission to intensive care unit, hysterectomy, blood loss of two liters or more, uterine inversion, near miss event as defined in the manual of operations)

• initiation of breastfeeding

• side effects such as nausea and abdominal pain

Once the cord is clamped and cut the drape will be placed under the woman's buttocks and blood loss measurement will begin. The blood loss measurement will continue for one hour regardless of whether the woman is kept in the delivery room or moved elsewhere. If the bleeding continues beyond one hour the blood loss measurement will continue until two hours postpartum.

Side effects will be recorded by the researcher. Any side effect requiring treatment will be regarded as an adverse event and a separate form will be filled.

Serious adverse events will be recorded in special forms and will be returned by the local investigators to the trial coordination unit within 24 hours.

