### Rationale for the non-inferiority hypothesis and for sample size estimation

The objective of this trial is to show 'non-inferiority' of the simplified package' compared to the full AMTSL package. As such, while superiority would be an added bonus it is not expected and is probably not plausible since the experimental intervention has fewer interventions.

In the conventional superiority trial, the aim is to determine whether one intervention is superior to another, for example, whether uterotonic is superior to nothing. By contrast, in a non-inferiority trial, the aim is to determine whether an alternative intervention with certain advantages is similar to a gold standard. The full AMTSL package represents the gold standard management strategy for reducing blood loss in the third stage of labour. In order to evaluate the effectiveness of a simplified package with fewer components that package has to be compared to the full package to see whether t is "non-inferior" to the gold standard [17].

Because proof of exact equality is impossible, a pre-stated margin of non-inferiority (Δ) for the difference in effectiveness has to be defined. The choice of the non-inferiority margin can be made using clinical assessment, which is to a certain extent arbitrary, and needs consensus among different stakeholders. A technique which has been proposed [17] to establish the non-inferiority margin is to look at the effect of the gold standard, in this case the full AMTSL, compared with placebo in historical (past) trials, in this case the expectant management. A reasonable criterion is to preserve 80% of the benefit of the full AMTSL package (considered as 100%) over expectant management (considered as 0%). Preserving a higher percentage (say 90%) will push the sample size calculations very high while a smaller percentage (say 50%) may not be considered acceptable.

Estimates of blood loss ≥ 1000 ml (severe PPH – sPPH) with active and passive management were taken from the literature. In addition, unpublished data from several ongoing WHO studies where postpartum blood loss is measured were obtained. Based on those data, a 1.5% risk of blood loss of 1000 ml with full active management was considered realistic and appropriate.

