The expectant management sPPH rate was more difficult to estimate because the data was only available from earlier published trials and blood loss estimation methods and the actual expectant management method differed between trials. Values between 3.0 to 4.0% are considered realistic and used for sample size estimations.

Table 1 includes different scenarios for the calculation of sample size, obtained by varying the sPPH rate with expectant management (3.0 to 4.0%) and varying the % retained effect (70% to 80%), assuming a fixed 1.5% sPPH rate for the full AMTSL package. These different scenarios result in different choices of the margin of non-inferiority **Δ**. The total sample size required for a non-inferiority test at the 2.5% level using a two-sided 95% confidence interval and a power of 80% is shown, as well as the power obtained for fixed sample sizes of 20,000 and 25,000.

**Table 1 T1:** Sample size scenarios

Blood loss ≥ 1000 ml with full amtsl	Blood loss ≥ 1000 ml with Expectant	Estimated impact of Full AMTSL	Proportion (of full AMTSL effect) retained by the simplified package	Δ (Difference to exclude to claim equivalence)	Total N for 80% Power	Power with total N = 20,000	Power with total N = 25,000
1.5	3.0	1.5	0.7	0.45	22,908	75%	83%

1.5	3.5	2.0	0.75	0.50	18,555	83%	90%

1.5	4.0	2.5	0.8	0.50	18,555	83%	90%

A trial of 22,908 women will have 80% power to show non-inferiority of the simplified package within 0.45% of the full AMTSL package sPPH rate (i.e. less than 1.95% sPPH rate), with a level of significance of 2.5% (Table 1, row 1). The estimates from the centres that have expressed interest in participating in the trial indicate that approximately 20,000–25,000 women can be recruited in a 12 months recruitment period. These centres have collaborated with WHO before and have experience in third stage trials.

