Randomization – Implementation	10	Who generated the allocation sequence, who enrolled participants, and who assigned participants to their groups.	4.4.2

Blinding (masking)	11	Whether or not participants, those administering the interventions, and those assessing the outcomes were blinded to group assignment. If done, how the success of blinding was evaluated.	4 (last sentence before 3.1)

Statistical methods	12	Statistical methods used to compare groups for primary outcome(s), *specifying whether a one or two-sided confidence interval approach was used*. Methods for additional analyses, such as subgroup analyses and adjusted analyses.	4.4.3 & 4.5

The actual management of third stage of labour will be recorded in all women to enable the analysis mentioned above.

Comparisons will be expressed as relative risks and risk differences with 95% confidence intervals. The analysis will be stratified by site, and if there is heterogeneity between the sites for any of the results possible causes of heterogeneity will be explored. In the presence of heterogeneity, the results will not be combined in a single summary estimate (or pooled estimate). In the absence of heterogeneity at the 5% level, the results will be combined.

The primary analysis will follow the following scheme for interpretation (Figure 1):[18] If the lower limit of the 95% confidence interval lies to the right of the non-inferiority margin (Δ) the experimental intervention will be declared "inferior" (situation H). Situations A-D indicate non-inferiority with respect to the pre-stated margin Δ. Situations E-G are inconclusive, although E and F are not likely to occur because the trial size guarantees sufficient power. If the results are inconclusive regarding the non-inferiority hypothesis and the whole 95% confidence interval lies to the right of zero (situation G), it will be concluded that the limited package was statistically significantly worse according to a superiority hypothesis.

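### Measurement of the primary outcome runs one hour or up to two on an unmasked judgement of continued bleeding, so ascertainment can differ by arm; a 60-minute reading would make this checkable

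*Protocol article*

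**What the plan says.** The abstract and the section Outcome measures define the primary outcome as "blood loss of 1000 ml or more at one hour and up to two hours for women who continue to bleed after one hour". Volume is read from a calibrated drape. The first hour applies to everyone: "The blood loss measurement will continue for one hour regardless of whether the woman is kept in the delivery room or moved elsewhere". The second hour is conditional: "If the bleeding continues beyond one hour the blood loss measurement will continue until two hours postpartum". The article gives no volume, rate or other criterion for continued bleeding and does not say who decides.

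Under Study design the protocol states: "The blinding of the intervention will not be possible because the comparison includes a manual procedure". No masked outcome assessor is described. The checklist in Table 2 has an item asking whether "those assessing the outcomes were blinded to group assignment", and its entry only refers back to the design section.

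The sample size section plans on "a 1.5% risk of blood loss of 1000 ml with full active management was considered realistic and appropriate". The margin is 0.45 to 0.50 percentage points.

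**The concern.** Cumulative blood loss cannot fall, so a second hour of measurement can turn a non-event into an event but never the reverse. Whether a woman gets that second hour depends on her course after randomization and on a judgement. That staff make it knowing the allocation is an inference from the lack of blinding and of any described masked assessor; the article does not say it in words.

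If staff extend measurement more readily in one arm, that arm gains events without any true difference. More extension in the simplified arm could block a true non-inferiority finding. Less extension there could produce a false one. The margin of 0.45-0.50 points corresponds to about 56-62 women per 12,500 (0.0045 x 12,500 = 56.25; 0.0050 x 12,500 = 62.5), so a few women per arm matter.

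**Working it through.** **Inputs from the protocol.** Event rate 1.5% with the full package; margin 0.45 or 0.50 points; one-sided 2.5%; total N of 22,908 or 18,555 for 80% power; recruitment target 25,000. Assumed, because they reproduce Table 1: 1.5% in both arms and 1:1 allocation.

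**Reproducing Table 1.** Total N = 2 x [2 x 0.015 x 0.985 x (1.960 + 0.842)²] / margin². This gives 22,907.1 at 0.45, rounded up to 22,908 (stated 22,908), and 18,554.8 at 0.50 (stated 18,555). At 25,000 women the standard error is √(2 x 0.015 x 0.985 / 12,500) = 0.1538 points. Power is Φ(0.45/0.1538 − 1.960) = 83.3% (stated 83%).

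**Who can be affected.** Only women below 1000 ml at one hour who would reach it by two. The protocol gives no figure for this share, so the following are assumptions:
- Two-hour loss X is log-normal with median m of 200-300 ml and P(X ≥ 1000) = 1.5%.
- The second hour adds a proportion g of 10-20% to the one-hour volume.

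Then σ = ln(1000/m)/2.170, and the share crossing in the second hour is 1.5% − P(X ≥ 1000(1+g)).

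Example, m = 200 and g = 10%: σ = 1.609/2.170 = 0.742; ln(1100/200)/0.742 = 2.299; upper tail 1.08%; share crossing 1.50 − 1.08 = 0.42%.

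| Median, ml | g | Rate at one hour, % | Crossing in second hour, % | Shift, 10-point arm gap | Shift, 20-point arm gap |
|---|---|---|---|---|---|
| 200 | 10% | 1.08 | 0.42 | 0.04 | 0.08 |
| 250 | 10% | 1.02 | 0.48 | 0.05 | 0.10 |
| 300 | 10% | 0.96 | 0.54 | 0.05 | 0.11 |
| 200 | 20% | 0.78 | 0.72 | 0.07 | 0.14 |
| 250 | 20% | 0.70 | 0.80 | 0.08 | 0.16 |
| 300 | 20% | 0.62 | 0.88 | 0.09 | 0.18 |

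Shifts are in percentage points: share crossing times the assumed arm difference in extension among these women. The upper rows are generous, since 0.88/1.5 = 58% of all events would first appear in the second hour.

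**Consequence of a 0.08-point shift** (10 women in 12,500) at 25,000 women and margin 0.45:
- Less extension in the simplified arm, true difference at the margin: the observed rates are 1.50% and 1.95 − 0.08 = 1.87%, with standard error 0.1628. Type I error = Φ(0.08/0.1628 − 1.960) = 7.1%. With the planning standard error of 0.1538 it is 7.5%.
- More extension in the simplified arm, no true difference: power = Φ((0.45 − 0.08)/0.1538 − 1.960) = Φ(0.446) = 67%.

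**Cross-check without the log-normal model.** If one arm misses 5% of its events because measurement stopped at one hour, type I error is 8.7% (simplified arm) or power is 69.5% (full-package arm) at the same N and margin. The order of magnitude agrees.

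**The case against.** The strongest reply is that the rule, applied as written, gives a two-hour cumulative loss for everyone: if bleeding has stopped at one hour, the one-hour and two-hour volumes are equal. Bias needs the rule to be applied differently by arm. This stands, and is why the bias is only possible.

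Next, the women who can cross are already heavy bleeders. In the model they have lost at least 909 ml at one hour and lose a further 91-100 ml (g = 10%), or at least 833 ml and a further 167-200 ml (g = 20%). Continued bleeding is hard to overlook in them, and nothing in the protocol supports a 10-20 point arm gap in that group. This also stands; the gap is purely illustrative.

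Third, the article is condensed and mentions a manual of operations, which may define continued bleeding. That would narrow the room for judgement, though the measurement time would still vary between women.

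A reader might go further in three ways that the document does not support:
- That the outcome has no fixed observation time at all. There is a one-hour floor, a two-hour ceiling and a calibrated drape.
- That no planned result could reveal a problem. Transfusion, and haemoglobin where feasible, do not depend on when drape measurement ends. They are partial checks.
- That the effect could approach the margin. Taking 1.5% as the one-hour rate and adding second-hour events on top gives shifts of up to 0.36 points. But 1.5% is the planning rate for an outcome that includes the second hour; placed there, the top of the range is 0.18.

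**Conclusion.** The point holds in limited form. The protocol lets the length of measurement depend on a judgement after randomization in an unblinded trial, and the article states no analysis at a time common to all women. Under the stated assumptions the shift is about 0.04-0.18 points against a margin of 0.45-0.50. It does not reach the margin, but its lower half is already enough to move the error rates noticeably: at 0.08 points, type I error of about 7-7.5% or power of about 67%.

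The loss distribution, the second-hour increment and the arm gap are all assumed, and the direction is unknown. The planned sample size reproduces and is not in question. This calls for a safeguard before recruitment, not for a different primary outcome.

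**What to change.** Keep the primary outcome as defined and add three things:

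1. Record the drape reading at 60 minutes in every woman, before anyone decides whether to go on measuring.
2. Pre-specify blood loss of 1000 ml or more at 60 minutes as a supportive sensitivity analysis, not as a second condition for claiming non-inferiority. State the caveat with it: the 60-minute rate is lower (0.62-1.08% in the model above), so the same absolute margin is easier to meet, and second-hour loss is ignored.
3. Report by arm the proportion of women whose measurement was extended beyond one hour.

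The cost is one extra reading on the form and one extra analysis. Sample size and power for the primary outcome are unchanged, and only measurement is affected. The reading must be on the form before recruitment starts, because it cannot be recovered afterwards.

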**Methods:**

A hospital-based, multicentre, individually randomized controlled trial is proposed. The hypothesis tested will be a non-inferiority hypothesis. The aim will be to determine whether the simplified package without CCT, with the advantage of not requiring training to acquire the manual skill to perform this task, is not less effective than the full AMTSL package with regard to reducing blood loss in the third stage of labour.

The simplified package will include uterotonic (oxytocin 10 IU IM) injection after delivery of the baby and cord clamping and cutting at approximately 3 minutes after birth. The full package will include the uterotonic injection (oxytocin 10 IU IM), controlled cord traction following observation of uterine contraction and cord clamping and cutting at approximately 3 minutes after birth. The primary outcome measure is blood loss of 1000 ml or more at one hour and up to two hours for women who continue to bleed after one hour. The secondary outcomes are blood transfusion, the use of additional uterotonics and measure of severe morbidity and maternal death.

We aim to recruit 25,000 women delivering vaginally in health facilities in eight countries within a 12 month recruitment period.

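### The primary outcome has two conflicting measurement windows, and staff who know the allocation decide whether the window runs to two hours

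*Protocol article*

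**What the plan says.** All references are to the protocol article.

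- **Start and end, first statement (Outcome measures).** Blood is collected in a calibrated drape and "measured from delivery to one hour following delivery or up to two hours if bleeding continues".
- **Start, second statement (same section).** "Once the cord is clamped and cut the drape will be placed under the woman's buttocks and blood loss measurement will begin". The next sentence has measurement continue for one hour, wherever the woman is.
- **Extension (same section).** "If the bleeding continues beyond one hour the blood loss measurement will continue until two hours postpartum". The article gives no other trigger.
- **Clamping time.** Both arms' Cord clamping sections tie clamping to an observed uterine contraction and add: "For practical purposes this is estimated to be around 1–3 minutes". The abstract's Methods instead has "cord clamping and cutting at approximately 3 minutes after birth" in both packages.
- **Placental delivery.** Full package: "Placenta will be delivered by controlled cord traction immediately after cord clamping and cutting". Simplified package: passive delivery, by gravity and maternal effort. The article states that "The two intervention packages will differ only in placental delivery technique".
- **Masking.** Study design says that the intervention cannot be blinded. The allocation section has the envelope opened in the second stage, before birth.

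**The concern.** The two statements define different quantities. One counts from birth. The other leaves out whatever is lost before the cord is clamped and the drape placed, and its one-hour end moves with the start. Centres in eight countries could follow either in good faith.

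The end of the window is also open to judgement. Whether a woman is measured for one hour or two depends on staff who know her allocation deciding that bleeding continues. The Background says that the third stage usually takes less than 10 minutes with controlled cord traction. It gives no duration for passive delivery, but that may take longer. A woman whose placenta is still undelivered at one hour, and who is not judged to be bleeding, would leave measurement at that point.

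The stake is a threshold outcome with an expected rate of 1.5%, tested against a fixed absolute margin of 0.45 to 0.50 percentage points. Small losses of events can move the conclusion.

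**Working it through.** **1. The windows side by side, in minutes after birth**

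- Counting from delivery: 0 to 60.
- Counting from clamping at 1–3 minutes and running one hour: 1–3 to 61–63.
- Starting at clamping but stopping one hour after delivery: 60 − 3 = 57 to 60 − 1 = 59 minutes of collection.
- The two-hour limit is counted from birth.

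The Analysis plan adds that, for newborn reasons, the cord may be cut straight after birth of the head. A start tied to clamping therefore also varies between women. No other section resolves the conflict.

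**2. Does the clamping rule differ by arm?** No. The two Cord clamping sections are worded identically, trigger included. On the plan as written, any gap before clamping is common to both arms.

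**3. Reproducing the plan's sample size.** Inputs from Table 1, row 1: 1.5% in both arms, margin 0.45 points, one-sided 2.5%, power 80%.

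n per arm = (1.96 + 0.8416)² × 2 × 0.015 × 0.985 / 0.0045² = 11,454, so the total is 22,908, as stated. The sample size is not in question.

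**4. Sensitivity to missed events.** The shares missed are assumptions; the article gives none. For the error rate, the true rates are set at the margin: full p₁ = 1.50%, simplified p₂ = 1.95%. If a share m of an arm's events is missed, that arm's observed rate is p(1 − m). With n per arm:

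SE = √[p₁(1 − p₁)/n + p₂(1 − p₂)/n], using observed rates

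False non-inferiority rate = Φ[(0.0045 − (p₂ − p₁))/SE − 1.96]

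- No loss: Φ(−1.96) = 2.5%.
- 5% missed in both arms, n = 11,454: rates 1.425% and 1.8525%, difference 0.4275 points, SE 0.1677 points. Φ(0.134 − 1.96) = 3.4%.
- 5% missed in the simplified arm only, n = 12,500: rates 1.50% and 1.8525%, difference 0.3525 points, SE 0.1624 points. Φ(0.600 − 1.96) = 8.7%.
- 5% missed in the full arm only, n = 11,454: rates 1.425% and 1.95%, difference 0.525 points, SE 0.1702 points. Φ(−0.441 − 1.96) = 0.8%.

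| Events missed | Arm affected | Error, N = 22,908 | Error, N = 25,000 |
|---|---|---|---|
| 5% | both | 3.4% | 3.4% |
| 10% | both | 4.6% | 4.7% |
| 5% | simplified only | 8.3% | 8.7% |
| 10% | simplified only | 21.4% | 22.9% |
| 5% | full only | 0.8% | 0.8% |
| 10% | full only | 0.2% | 0.2% |

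Loss in the full arm only costs power instead. With both true rates at 1.5% and N = 22,908, 5% missed gives an observed difference of 0.075 points and SE 0.1586 points. Power is then Φ(2.364 − 1.96) = 65.7%, down from 80%.

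**The case against.** A reader might infer that the plan under-counts blood loss in the simplified arm and so is biased toward non-inferiority. The documents do not support that.

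- Clamping in the simplified arm has a prompt, the observed contraction, and it is the same as in the full arm.
- The direction could run the other way. In the full arm, traction starts just when the drape is to be placed, so loss could be missed there. If passive delivery is slower, more simplified-arm women may be bleeding at one hour and be measured longer, which adds events to that arm.
- The outcome is total loss. Women still bleeding at one hour are already followed to two hours, with or without a delivered placenta. The gap is limited to women not judged to be bleeding at one hour who pass 1000 ml later, and nothing shows how many there are.
- The drape yields a measured volume, so judgement affects only when measurement starts and stops.
- A working criterion for continued bleeding, and the time fields, may be in the manual of operations or the data forms. Their absence from a condensed article is no fault. The Analysis plan already says that actual third-stage management is recorded for all women.
- Starting collection after clamping is defensible, since amniotic fluid in the drape would count toward a fixed 1000 ml threshold.

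All of this stands, and it limits the point. It does not remove the contradiction about the window, which lies within one section, or the dependence of the window's length on an unmasked judgement. Nor is loss shared by both arms harmless: it shrinks the absolute difference against a fixed absolute margin.

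**Conclusion.** The point holds as an inconsistency in the primary outcome's measurement window, together with room for differential measurement at its end. Under-counting in one arm is possible but not shown, and its direction is not fixed.

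The pattern closest to the identical clamping rule is loss shared by both arms. Its effect is modest: 2.5% becomes about 3.4% if 5% of events are missed. The 8.7% figure (25,000 women) applies only if 5% are missed in the simplified arm and none in the full arm. All these figures rest on assumed shares, true rates of 1.50% and 1.95%, a 0.45-point margin and a normal approximation. They show how sensitive the test is and do not estimate a bias. The definition should be settled because the margin is narrow and the remedy is cheap.

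**What to change.** 1. Reconcile the Outcome measures statements to one start and one end of measurement, the same in both arms. Whether the start is birth or clamping is a trade-off between losing the first minutes and letting amniotic fluid into the drape, and the choice should be stated.
2. Record the times of birth, clamping, drape placement and placental delivery, so that capture can be compared between arms.
3. Read the drape at 60 minutes in every woman, including those measured longer. Report the 1000 ml outcome at that fixed time as a check free of the unmasked extension.
4. Continue measurement to two hours also when the placenta is undelivered at one hour.
5. Reconcile the clamping times in the abstract and the Cord clamping sections. Which is right is for the sponsor to decide.

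The cost is wording in the protocol, manual and forms, slightly more recording, and a few women measured for longer. The sample size does not change.
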